#### Exclusion Criteria

Lethal congenital anomalies or obvious syndromeBleeding diathesis (abnormal coagulation screen/platelet < 100,000/ mm^3^)The presence of Intraventricular haemorrhage.Diastolic Hypotension (defined as a diastolic blood pressure less than the 3rd centile for any given gestation) unresponsive to medical treatment (≥30 mL/kg fluid bolus and ≥ 2 inotropes)Hypoxic-ischemic encephalopathy undergoing therapeutic hypothermiaEvidence of renal impairment (Creatinine >100 micromol/l)Severe Hypovolaemia: Heart rate > 180, capillary refill > 5 s, urine output < 0.5 ml/kg/hour, in addition to diastolic hypotension mentioned above.

#### Intervention

Infants in the intervention arm will receive an intravenous loading dose of milrinone lactate injection (10 mg/10 mL) at a dose of 50 μg/kg administered over 60 min followed by a maintenance infusion, beginning at 0.375 μg/kg/min to a maximum 0.750 μg/kg/min. The duration of therapy is until discontinuation of iNO or a maximum of 35 h in adherence with the summary of product characteristics (SmPC) recommendation. A 10 mL/kg bolus of normal saline will be administered with the milrinone bolus over the same 1 h period.

A loading dose was chosen to ensure the rapid attainment of therapeutic blood concentrations. The slow rate of administration was chosen to minimize the risk of infusion-related adverse effects, such as hypotension. This dosing regimen was established following the recent pharmacokinetic study performed by our group and described above [27]. Dose increase will be performed in response to the need for oxygen (FiO_2_) to maintain adequate pre-ductal saturations (95% or greater). Dose incrementation will be carried out every 2 h following the bolus if the fall in FiO_2_ needed to maintain an adequate saturation is less than 20%. Dose escalation will be carried out as described below (Section “Product and placebo preparation and infusion regimen”). For example, if 2 h after administration, the FiO_2_ of an infant falls from 60 to 45% (< 20%) to maintain a saturation of 95% or greater, the rate of infusion will be increased based on the table below. This escalation will continue every 2 h until a reduction of FiO_2_ of 20% or greater is achieved down to 40% FiO_2_. The maximum dose will be 0.750 μg/ kg/min.

#### Control

Infants in the control arm will receive an intravenous loading dose of placebo (normal saline) at a rate equivalent to the infusion rate of the milrinone bolus, administered over 60 min. A bolus of normal saline of 10 ml/kg will accompany the placebo infusion, as per the intervention arm. Following the loading protocol, a saline infusion running at a rate similar to the milrinone infusion will be commenced for a maximum period of 35 h or until discontinuation of iNO if it occurs sooner. The saline infusion will be titrated up in increments similar to the milrinone infusion.

#### Product and placebo preparation and infusion regimen

The proposed placebo is an authorised product in the EU- see PA below.We will prepare the product in line with the instructions in the SPC. The outline below will be included in the protocol as suggested. The product will be diluted with solutions specified in section 6.6 of the SPC. A milrinone infusion solution containing 200 micrograms/ml will be prepared by diluting 10 ml of Primacor injection with 40 ml of 0.9% sodium chloride (Baxter Sodium Chloride 0.9% *w*/*v* Intravenous Infusion BP 100 ml- PA 0167/008/015). The syringe will be inverted at least 10 times to ensure adequate mixing. Each infusion syringe will be freshly prepared before use. The prepared infusion will be visually inspected for particulate matter or discolouration. The diluted solution will be used within 1 h of preparation.

The placebo infusion will consist of 50 ml of the diluent (Baxter Sodium Chloride 0.9% w/v Intravenous Infusion BP 100 ml- PA 0167/008/015). Each placebo infusion syringe will be freshly prepared before use. The prepared placebo infusion will be visually inspected for particulate matter or discolouration. Administration rates will be guided by the SPC:

**Table Taba:** 

**Primacor Injection Dose (μg/kg/min)**	**Infusion Delivery Rate (ml/kg/hr)**
0.375	0.11
0.400	0.12
0.500	0.15
0.600	0.18
0.700	0.21
0.750	0.22

#### Use of additional inotropic and concomitant therapy

The most common co-morbidity accompanying pulmonary hypertension in term infants is hypotension. The approach to managing systemic hypotension will be as follows:Systolic hypotension (defined as a systolic BP < the 3^rd^ centile for any given gestation) will be treated with a bolus of saline (10 ml/kg) followed by adrenaline at a dose of 0.05 μg/kg/min up to 2 μg/kg/min.Diastolic hypotension (defined as a diastolic BP < the 3^rd^ centile for any given gestation) will be treated with a bolus of saline (10 ml/kg) followed by dopamine at a dose of 5 μg/kg/min up to a maximum of 20 μg/kg/min.

Infants failing to respond to the above interventions will be withdrawn from the study and un-blinded (see below). Dobutamine will not be used during the study period due the risk of hypotension when used concomitantly with milrinone. Adrenaline/noradrenaline will be used as second line agents. Steroids will be used for severe hypotension/shock at a dose of 1 mg/kg 6 hourly IV.

If required, infants will be sedated with fentanyl (rather than morphine) to avoid the risk of hypotension. The starting dose of the fentanyl infusion is 1.0 μg/kg/min following a bolus of 1.0 μg/kg. Management of all other aspects of pulmonary hypertension will be at the discretion of the attending neonatologist based on unit policies. Other pulmonary vasodilator agents such as sildenafil, prostacyclin and/or bosentan will not be used during the study period.

Other considerations:

Aminophylline/Caffeine: aminophylline/caffeine may compete with milrinone for phosphodiesterase inhibition and therefore may attenuate the clinical effect. However, aminophylline/caffeine administration is not used in infants with PPHN and therefore the risk of co-administration is low. None-the-less, we will exclude patients with concomitant administration from the study.Frusemide or bumetanide will not be administered in intravenous lines containing milrinone lactate in order to avoid precipitation.Milrinone will not be diluted with sodium bicarbonate.As outlined below in the monitoring section (Monitoring, outcome measures and participant timeline): hypokalaemia will be monitored and corrected in advance of/and during milrinone use as diuresis secondary to improved cardiac output may ensue following milrinone administration.Calcium channel blockers (CCB) are not used in neonates and therefore the potential interaction between milrinone and CCBs is not a concern in this study.

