#### Exit criteria

The following criteria will mandate the discontinuation of the intervention in both arms and a return to standard of care, as these are considered side effects of the medication if they occur within 1 to 3 days of administration of the medication: profound hypotension requiring > 30 mL/kg fluid bolus and inotropic support of ≥20 mcg/kg/min of intravenous dopamine or dobutamine, thrombocytopenia of ≤100,000/mm3, and arrhythmia requiring treatment.

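### Two unaligned rules for refractory hypotension: one withdraws and un-blinds the infant, the other only stops study drug, counts a barred drug and omits adrenaline

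*Protocol article*

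**What the plan says.** Protocol article, Use of additional inotropic and concomitant therapy, sets two treatment pathways. Systolic hypotension "will be treated with a bolus of saline (10 ml/kg) followed by adrenaline at a dose of" 0.05 μg/kg/min, rising to 2. Diastolic hypotension "will be treated with a bolus of saline (10 ml/kg) followed by dopamine at a dose of" 5 μg/kg/min, with a ceiling of 20. The next sentence gives the consequence of failure: "Infants failing to respond to the above interventions will be withdrawn from the study and un-blinded (see below"). The same section then adds three statements without placing them before or after that step: "Dobutamine will not be used during the study period", "Adrenaline/noradrenaline will be used as second line agents" and "Steroids will be used for severe hypotension/shock at a dose of" 1 mg/kg every 6 hours.

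Protocol article, Exit criteria, lists events that "will mandate the discontinuation of the intervention in both arms and a return to standard of care". The hypotension event is profound hypotension needing more than 30 mL/kg of fluid together with "inotropic support of ≥20 mcg/kg/min of intravenous dopamine or dobutamine". That section mentions neither withdrawal from the study nor un-blinding.

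Two other sections bear on the consequence. Concealment and blinding keeps families, care providers, data collectors, echocardiographers, primary outcome assessors and analysts unaware of allocation. Statistical methods applies intention to treat to everyone enrolled, including infants who stop treatment for whatever reason.

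**The concern.** The two sections describe the same clinical event with different criteria and different consequences. Under one, the infant leaves the study and the code is broken. Under the other, study drug stops and usual care resumes, which needs no knowledge of the allocation.

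The event is foreseeable. The therapy section itself names hypotension as the commonest accompanying problem. The group's own observational data, summarised in the Introduction, show mean blood pressure falling after milrinone (largest effect at 6 h), with more vasoactive inotrope use at 6 and 24 h. The same data show pressure rising again after 12 h while inotrope use fell. Hypotension and inotrope use are both named under Secondary objective, so the exit rule acts on something that treatment may affect.

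At stake are the blind and the clarity of follow-up in a trial of 20 infants whose primary outcomes are time on iNO and time on invasive ventilation. The section on the relevance of the primary outcome also makes refining the discontinuation criteria a pilot aim. That is harder if exits are recorded under two rules.

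**Working it through.** There is no stated figure to reproduce. The check is a side-by-side reading plus simple arithmetic on fluid.

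| Element | Use of additional inotropic and concomitant therapy | Exit criteria |
|---|---|---|
| Fluid | 10 mL/kg per pathway; repetition not addressed | more than 30 mL/kg |
| Dopamine | up to 20 μg/kg/min (diastolic pathway) | 20 μg/kg/min or more |
| Adrenaline | up to 2 μg/kg/min (systolic pathway) | not counted |
| Dobutamine | barred | counted |
| Trigger | failure to respond | support was required |
| Consequence | withdrawn and un-blinded | intervention stopped |

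**Dopamine.** The limit is the same in both places: 20 against 20.

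**Fluid.** Give each printed bolus once. One pathway gives 10 mL/kg; both give 10 + 10 = 20. Counting the 10 mL/kg of saline that accompanies the loading dose in both arms (Intervention, Control), these become 20 and 30. None exceeds 30. This holds only if boluses are not repeated, which the text does not settle.

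**Illustrative profiles.** These are constructed to locate disagreements; they are not frequencies. A to C take each bolus once, and D and E assume repeat boluses. The result is the same whether or not the loading saline is counted.

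- A. Systolic pathway only, adrenaline 2, no response, 10 or 20 mL/kg: meets the therapy-section rule, not Exit criteria. At 40 or 50 mL/kg the answer is unchanged, because neither dopamine nor dobutamine was given.
- B. Diastolic pathway only, dopamine 20, no response, 10 or 20 mL/kg: meets the therapy-section rule, not Exit criteria.
- C. Both pathways, dopamine 20 and adrenaline 2, no response, 20 or 30 mL/kg: meets the therapy-section rule, not Exit criteria.
- D. Dopamine 20, 40 or 50 mL/kg, pressure recovers: meets Exit criteria only.
- E. As D, without recovery: meets both, with different consequences.

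If boluses may be repeated past 30 mL/kg, B and C join E and meet both rules. A does not move. The adrenaline omission is therefore the criterion mismatch that no fluid assumption removes.

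**Effect of the cross-reference.** If the pointer to later text means that Exit criteria supplies the cut-off for non-response, the fluid and trigger differences disappear. The barred dobutamine, the missing adrenaline and the different consequence remain.

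**Scale.** With 10 infants per arm (Sample size), one infant classified differently is 1/10 = 10 percentage points of an arm's exit rate, and 1/20 = 5% of the trial.

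**The case against.** The best defence is that both sections bind and serve different purposes. One manages hypotension and deals with non-response; the other lists drug-attributed side effects that end treatment. An infant may meet one and not the other without contradiction, and where both apply, withdrawing and un-blinding already includes stopping the drug. In all five profiles at least one rule takes the infant off study drug. This stands, and it limits the finding.

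Repeat boluses also look intended. Exclusion Criteria describes unresponsive diastolic hypotension in terms of at least 30 mL/kg, and Exit criteria uses more than 30. So the fluid difference may be only apparent. This stands too.

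Dobutamine is joined to dopamine by *or*, so the dopamine limb works even if dobutamine is never given. That is true of dobutamine, but it does nothing for the adrenaline-treated infant.

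Finally, breaking the code in refractory hypotension is an ordinary safety exception, and the pointer to later text may refer to a procedure in the full protocol that the article condenses. The absence of an un-blinding procedure is accordingly not held against the plan. But the printed sentence attaches un-blinding to non-response itself, with no test of whether knowing the allocation would change care. That is a rule stated badly, not a detail left out.

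**Conclusion.** The point holds as a misalignment between two printed rules. Whatever is assumed about fluid or the cross-reference, three defects remain: the consequences differ; the exit criterion counts a barred drug and omits the prescribed one; and the order of withdrawal, second-line agents and steroids is unstated. An infant treated with adrenaline alone can leave only through withdrawal and un-blinding.

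Three stronger readings are tempting, and the documents do not support them.

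- A reader might infer a safety gap that leaves adrenaline-treated infants on drug. The therapy section covers them: non-response means withdrawal. A gap would arise only if Exit criteria were taken to replace that rule, which the text does not say.
- A reader might infer a firm contradiction over fluid volume. That needs boluses to be given once only, which is not stated.
- A reader might infer lost primary-outcome data and bias. That needs withdrawal to mean the end of follow-up. The intention-to-treat statement points the other way, so this is an ambiguity and not a demonstrated loss.

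The number of infants affected and the size of any bias cannot be computed from the documents. The 10 percentage points per infant conveys scale only. The tension between automatic un-blinding and the blinding plan is real but likewise unquantified.

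**What to change.** Use one hypotension exit criterion, worded identically in both sections:

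- one cumulative fluid volume, stating whether boluses may be repeated and whether the loading saline counts;
- a dopamine limit or an adrenaline limit, with dobutamine removed;
- its place relative to second-line agents and steroids.

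The investigators set the thresholds, and should check them against Exclusion Criteria so that no eligible infant already meets the criterion at entry.

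Give it one consequence, replacing the withdraw-and-un-blind sentence with text such as:

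> When an infant meets the hypotension exit criterion, study drug is stopped and usual care resumes. The infant remains in the trial, outcomes are collected to discharge, and the analysis is as randomised. The blind is broken only if knowing the allocation would change care; the reason and the people informed are recorded. Outcome assessors, echocardiographers and analysts remain blinded.

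The cost is one short amendment to the regulators and ethics committees, a route that Ethics, dissemination already provides for. It needs no extra infants or procedures, and emergency code-break remains available.

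### The two hypotension stopping rules disagree on the drugs that count and on whether the infant leaves the study or only stops study drug

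*Protocol article*

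**What the plan says.** The section on use of additional inotropic and concomitant therapy sets out two treatment pathways. Systolic hypotension "will be treated with a bolus of saline (10 ml/kg) followed by adrenaline", at 0.05 up to 2 μg/kg/min. Diastolic hypotension "will be treated with a bolus of saline (10 ml/kg) followed by dopamine", at 5 up to 20 μg/kg/min. For non-response it says: "Infants failing to respond to the above interventions will be withdrawn from the study and un-blinded (see below"). It then adds "Dobutamine will not be used during the study period due the risk of hypotension when used concomitantly with milrinone" and "Adrenaline/noradrenaline will be used as second line agents".

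The Exit criteria section gives a second rule. Its hypotension limb is "profound hypotension requiring > 30 mL/kg fluid bolus and inotropic support of ≥20 mcg/kg/min of intravenous dopamine or dobutamine". Meeting any exit criterion will "mandate the discontinuation of the intervention in both arms and a return to standard of care". That section does not mention adrenaline, withdrawal from the study or un-blinding.

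The Statistical methods section commits to an intention-to-treat analysis of every enrolled infant, including those who stopped treatment for whatever reason. The Sample size section sets 10 infants per arm, 20 in all.

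**The concern.** Both sections tell a site what to do when blood pressure cannot be held, and both are current text. If they disagree, the infant's status in the trial depends on which one the site follows: out of the study and un-blinded, or off study drug and still in.

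That status determines the data. Time on iNO and time on invasive ventilation are the primary outcomes, and both continue to accrue after study drug stops. Blood monitoring is scheduled to 24 h after discontinuation. The incidence of hypotension is a stated secondary comparison, and the rate of loss to follow-up is something the pilot sets out to learn. An intention-to-treat analysis needs outcomes from infants who stop early, and the wording that withdraws them from the study may end collection.

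The drug mismatch matters because a mandatory exit criterion should be reachable by the treatments the protocol prescribes. Adrenaline is the prescribed drug for systolic hypotension, and the exit criterion does not recognise it.

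**Working it through.** The article gives no figure to reproduce, so the check sets the two rules side by side.

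| Item | Additional inotropic therapy section | Exit criteria section |
|---|---|---|
| Fluid | a 10 ml/kg saline bolus in each pathway; repeats neither scheduled nor barred | more than 30 mL/kg |
| Systolic drug | adrenaline, up to 2 μg/kg/min | none named |
| Diastolic drug | dopamine, up to 20 μg/kg/min | dopamine, 20 or more |
| Dobutamine | barred during the study | counts towards exit at 20 or more |
| Consequence | withdrawn from the study and un-blinded | intervention stopped, standard of care |

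**Drugs.** The exit criterion names 2 agents. One is barred, so 2 − 1 = 1 is usable: dopamine. Its permitted range is 5 to 20 and the criterion is 20 or more, so the two overlap only at exactly 20. There is no conflict on the dopamine level itself.

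**Adrenaline without dopamine.** The hypotension limb joins fluid and inotrope with *and*, so both parts must be met. An infant on adrenaline with no dopamine receives 0 mcg/kg/min of either named agent. Since 0 < 20, the limb is not met at any adrenaline dose, including the maximum of 2. Two limits apply. The infant could still exit for thrombocytopenia or arrhythmia. It could also meet the hypotension limb later if dopamine reached 20 with enough fluid.

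**Fluid.** With one bolus per pathway and the 10 mL/kg saline given with the loading dose in both arms:

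- one pathway: 10 + 10 = 20 mL/kg
- both pathways: 10 + 10 + 10 = 30 mL/kg, which is not more than 30

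If boluses are repeated, the exit volume is reached at 4 treatment boluses (4 × 10 = 40), or at 3 if the loading-dose saline counts (10 + 3 × 10 = 40). Because repeats are not barred, the text does not settle which rule is reached first. The Exclusion Criteria describe hypotension unresponsive to treatment as at least 30 mL/kg of fluid and at least 2 inotropes. That is an eligibility rule, but it suggests the authors do not think of non-response as failure after 10 mL/kg.

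**Consequence.** Stopping the intervention fits an intention-to-treat analysis that includes infants who stopped treatment. Withdrawal from the study leaves open whether their outcomes are still collected.

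**Scale of one infant.** 1/10 = 10% of an arm; 1/20 = 5% of the trial. These are the weight of a single infant, not an estimate of how many would be affected.

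**The case against.** The best defence is that the two sections are one rule loosely described. The withdrawal sentence points to something below it, the exit section follows, and an exit with return to standard of care could be what withdrawal was meant to convey. On that reading, silence about un-blinding in the exit section is not a contradiction. The article also says that the pilot aims to refine its criteria for stopping therapy, so they are openly provisional. The analysis plan already keeps every enrolled infant, and hours on iNO and ventilation are routine chart data that nothing says will stop being collected.

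Much of this stands, and it limits the point. It does not remove it. If the exit section defines failure, then failure of adrenaline is undefined and a barred drug still counts as a trigger. A provisional rule still has to be applied alike across three centres if it is to be refined. And an intention-to-treat commitment needs the data that withdrawal from the study, read literally, may cut off.

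Several stronger readings are tempting, and the document does not support them:

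- **A safety gap.** A reader might infer that an infant failing maximal adrenaline has no stopping rule. The additional-therapy section still removes that infant.
- **Conflicting fluid thresholds.** Repeat boluses are not barred, so a difference is not established.
- **Adrenaline listed inconsistently as first and second line.** It can be first line for systolic hypotension and second line after dopamine for diastolic hypotension, which is coherent.
- **Missing un-blinding detail or steroid timing.** A condensed article may leave these to the full protocol. Un-blinding after failed rescue can be justified.
- **Bias towards one arm, or un-blinded assessors and analysts.** Nothing in the text shows either. iNO weaning is standardised, which limits any effect on that outcome, although "Management of all other aspects of pulmonary hypertension will be at the discretion of the attending neonatologist based on unit policies".

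**Conclusion.** The point holds as an internal inconsistency. The hypotension exit criterion relies on a drug that the protocol bars and leaves out the drug that it prescribes for systolic hypotension. The consequences are also worded differently, and study withdrawal sits badly with the planned intention-to-treat analysis. The drug mismatch is plain on the text. The threat to the data is conditional: it rests on withdrawal from the study being taken at its ordinary meaning, so that follow-up may end.

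The number of infants affected and the direction of any bias cannot be computed from the article. In a trial of 20, each infant lost to follow-up this way would be 10% of its arm, which is enough to make a wording correction worthwhile.

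**What to change.** Use one hypotension stopping rule in both sections:

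- Remove dobutamine from the exit criterion. Add failure of maximal adrenaline (2 μg/kg/min) for systolic hypotension beside dopamine at 20 μg/kg/min.
- State one fluid volume, set by the investigators, and leave clinicians free to stop study drug earlier.
- Replace withdrawal from the study with: study drug stopped, the treating clinician un-blinded if care requires it, outcome collection continued, and the infant kept in the intention-to-treat analysis.

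Parents' right to withdraw their infant, given in the ethics section, is unaffected.

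The cost is minor rewording and continued routine data collection in any infant who stops study drug. The unified fluid volume may differ from what one section now says, and under some readings it would move a threshold. The investigators should therefore choose it on clinical grounds and not treat it as an editorial change.

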### The relevance of the primary outcome

iNO use is expensive and currently requires invasive ventilation. Invasive ventilation can cause baro- and volutrauma, may lead to parenchymal lung damage and the evolution of pneumothoraces. Ventilation is often accompanied by the administration of sedative agents such as morphine and midazolam. In addition, prolonged ventilation will delay bonding with parents, delay feeding and suckling and will lead to prolonged hospitalisation. A reduction in the time spent invasively ventilated will (in addition to the other benefits outlined above) reduce hospital stay, promote earlier enteral nutrition, parental bonding, breast feeding and significantly reduce healthcare costs.

The purpose of this pilot study is to assess the feasibility of performing a pivotal trial and to obtain preliminary data to calculate a sample size for a definitive multi-centre trial of milrinone therapy in PPHN. We aim to recruit a total of 20 infants with PPHN (10 receiving milrinone and 10 receiving placebo) over a 4-year period. We then plan to seek additional funding in order to facilitate the running of the multicentre RCT in European and North American centres. In this pilot study we also aim to ascertain issues with recruiting infants and obtaining consent, compliance with the protocol, the rate (if any) of loss to follow up, and the general acceptability, feasibility and compliance of administering the intervention. This number will also allow us to calculate a standard deviation which will be used in a sample size calculation for the full-scale trial. In addition, we aim to refine the criteria for discontinuing therapy which are outlined below.

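### The printed fentanyl starting infusion repeats the whole bolus every minute (60 μg/kg/h); it is probably a unit error and must be verified and, if wrong, corrected

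*Protocol article*

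**What the plan says.** The protocol article, under Use of additional inotropic and concomitant therapy, names fentanyl as the sedative when one is needed: "infants will be sedated with fentanyl (rather than morphine) to avoid the risk of hypotension". It then fixes the dose: "The starting dose of the fentanyl infusion is 1.0 μg/kg/min following a bolus of 1.0 μg/kg". This is the only fentanyl dosing in the article. There is no maximum rate, no titration rule, no syringe concentration and no second figure against which the first could be checked.

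The same section gives its inotropes per minute. Adrenaline is "followed by adrenaline at a dose of 0.05 μg/kg/min up to 2 μg/kg/min", and dopamine is "followed by dopamine at a dose of 5 μg/kg/min up to a maximum of 20 μg/kg/min".

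The only other regimen in the article that sets a drug bolus followed by an infusion of the same drug is milrinone, under Intervention: "at a dose of 50 μg/kg administered over 60 min followed by a maintenance infusion, beginning at 0.375 μg/kg/min to a maximum 0.750 μg/kg/min".

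**The concern.** The bolus and the infusion carry the same number, 1.0, and differ only in the time unit. Read literally, the infusion gives the whole bolus again in its first minute and in every minute after that. A bolus that size adds almost nothing before such an infusion, which suggests that the time unit is wrong. The neighbouring inotrope doses are in μg/kg/min, so a unit carried over from them is plausible, though not shown.

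The line is a dosing instruction for an opioid in newborns. The article leaves other aspects of pulmonary hypertension management to the attending neonatologist, but it specifies the sedative and its starting dose itself, for both arms. Use is conditional on need, but that need is unlikely to be rare. Every enrolled infant is on iNO (Eligibility criteria), and The relevance of the primary outcome says: "iNO use is expensive and currently requires invasive ventilation". It adds: "Ventilation is often accompanied by the administration of sedative agents such as morphine and midazolam".

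What is at stake is the safety of the sedated infants. No bias between arms is alleged.

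**Working it through.** **Inputs, all from the protocol article**

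- Fentanyl: bolus 1.0 μg/kg, starting infusion 1.0 μg/kg/min (Use of additional inotropic and concomitant therapy).
- Milrinone: load 50 μg/kg, maintenance 0.375 to 0.750 μg/kg/min (Intervention).
- Weights: 2.0 kg, the minimum birth weight (Eligibility criteria), and 3.481 kg, the mean birth weight in the earlier study of 11 infants (Pharmacokinetics of milrinone in PPHN).

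The article gives no derivation of the fentanyl rate, so there is no calculation of the plan's to reproduce. The check is a unit conversion and a comparison of each bolus with its own infusion.

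**Step 1. Fentanyl as printed**

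- Hourly rate: 1.0 × 60 = 60 μg/kg/h.
- Bolus in minutes of infusion: 1.0 ÷ 1.0 = 1 min.
- Bolus as a share of bolus plus first infusion hour: 1 ÷ (1 + 60) = 1.6%.
- At 2.0 kg: bolus 2.0 μg, then 2.0 × 60 = 120 μg/h.
- At 3.481 kg: bolus about 3.5 μg, then 3.481 × 60 = 208.9 μg/h.

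**Step 2. Milrinone, for comparison**

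- Load in minutes of maintenance: 50 ÷ 0.375 = 133 min; 50 ÷ 0.750 = 67 min.
- First infusion hour: 0.375 × 60 = 22.5 μg/kg; 0.750 × 60 = 45 μg/kg.
- Load as a share of load plus first infusion hour: 50 ÷ 72.5 = 69%; 50 ÷ 95 = 53%.

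**Step 3. Fentanyl if the rate was meant per hour (assumption)**

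- Per minute: 1.0 ÷ 60 = 0.0167 μg/kg/min.
- Bolus in minutes of infusion: 1.0 ÷ (1.0 ÷ 60) = 60 min.
- Bolus share: 1 ÷ (1 + 1) = 50%.
- Printed rate relative to this: 60 ÷ 1 = 60-fold.

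| Regimen | Bolus in minutes of infusion | Bolus share of bolus plus first hour |
|---|---|---|
| Fentanyl as printed | 1 | 1.6% |
| Fentanyl if per hour (assumption) | 60 | 50% |
| Milrinone at 0.750 μg/kg/min | 67 | 53% |
| Milrinone at 0.375 μg/kg/min | 133 | 69% |

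The two columns express one ratio in two ways and are not separate pieces of evidence.

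**Step 4. Are the milrinone units sound?** The infusion table under Product and placebo preparation and infusion regimen can be recomputed as dose × 60 ÷ 200 μg/ml. This gives 0.1125, 0.12, 0.15, 0.18, 0.21 and 0.225 ml/kg/h against the printed 0.11, 0.12, 0.15, 0.18, 0.21 and 0.22. The table agrees to rounding, so the milrinone comparison rests on consistent units.

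**The case against.** The strongest reply is that the article does not contradict itself. It prints one bolus and one rate, and converting the rate to an hourly figure only restates it. To show that 60 μg/kg/h is wrong would take a fentanyl reference range, and the article has none. The milrinone comparison cannot supply one: the relation of load to maintenance depends on a drug's volume of distribution and clearance, which the article reports for milrinone only. The article also explains why milrinone is loaded but gives no purpose for the fentanyl bolus. The carried-over unit is conjecture. Finally, fentanyl is conditional, common to both arms and not the study drug, and the full protocol may already have the right figure.

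Much of this stands. The milrinone ratio is illustrative, the intended unit is unknown, and the 60-fold figure depends wholly on the per-hour assumption. No sum in the article fails, so this is a suspected unit slip and not a failed calculation.

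It does not remove the point. A bolus worth one minute of the infusion that follows it is implausible on its face, without any comparator. Misreading of the PDF is not a convincing explanation, since *min* in place of *h* is not a typical extraction fault. Nor is this a detail left to another document: the article prints the dose as an instruction. That both arms receive it rules out an obvious bias but does not make it safer.

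**Conclusion.** The concern holds. As printed, the starting infusion is 60 μg/kg/h and repeats the full bolus every minute, and nothing in the article corrects or explains it. It is probably a unit error; confidence in that inference is medium, because the article never states the intended unit. If per hour was intended, the printed rate is 60 times too high. If the printed unit is right, the factor is 1 and the line needs only confirmation.

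This must be settled because it is an opioid dosing line for newborns, not because a dosing error has been proven. The article gives no sedation rate and no fentanyl pharmacology, so neither the number of infants exposed nor a clinical effect is estimated. Whether the operative documents carry the same figure cannot be told from the article. Sample size, error rate and analysis are not affected.

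**What to change.** Check the fentanyl unit and value against the full protocol and the pharmacy orders at all three sites. What follows depends on the result:

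- **The printed unit is right:** record the confirmation. Nothing else is needed.
- **Only the article is wrong:** publish a correction of that line.
- **The operative documents carry the same wrong figure:** amend them and notify all sites before fentanyl is used further under the protocol.

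No replacement dose is proposed here, because the article gives no basis for one. The cost is one document check, plus a published correction if the line is wrong. A clarifying amendment and site notice are needed only in the third case.
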